## Abstract

**Background:**

Adequate intake of macro- and micronutrients and adoption of an active lifestyle during pregnancy are essential for optimum maternal and fetal health and offspring development. Dietary counseling and advice regarding adequate physical activity are integral components of antenatal care. Personalized coaching through the use of mobile health (mHealth) that supports behavior modification is an innovative approach that needs exploration.

**Objective:**

Our primary aim is to assess the efficacy of an mHealth program in improving diet, supplement use, and physical activity during pregnancy. Secondary objectives include evaluation of the program’s effect on maternal and offspring health outcomes and assessment of its compliance and usability.

**Methods:**

A randomized controlled trial was initiated at the Aga Khan University Hospital in Karachi, Pakistan, in January 2020. We aim to recruit 300 pregnant women in their first trimester who have smartphones, do not have comorbidities, and are not taking medications. The intervention group will be trained to use an mHealth app called *PurUmeed Aaghaz*. Through this app, the subjects will report information about their diet, supplement use, and physical activity and will receive personalized advice and three push messages as weekly reminders. The research assistant will obtain similar information from the control group via a paperless questionnaire; this group will receive standard face-to-face counseling regarding diet, supplement use, and physical activity. Data will be collected at enrollment and during four follow-up sessions scheduled 6 weeks apart. Primary study outcomes include improvements in diet (ie, change in mean dietary risk score from baseline to each follow-up), supplement use (ie, changes in mean supplement use score and biochemical levels of folic acid, iron, calcium, and vitamin D on a study subset), and mean duration of reported physical activity (minutes). Secondary study outcomes relate to maternal health (ie, gestational diabetes mellitus, gestational hypertension, pre-eclampsia, and gestational weight gain), newborn health (ie, birth weight and length and gestational age at delivery), and infant health (ie, BMI and blood pressure at 1 year of age). Compliance will be determined by the proportion of participants who complete the 6-month coaching program. Usability will be assessed based on features related to design, interface, content, coaching, perception, and personal benefit.

**Results:**

The study was approved by the Ethics Review Committee of the Aga Khan University in 2017. The recruitment of study participants was completed in September 2021. All follow-ups and outcome assessments are expected to be completed by March 2023 and analysis is expected to be completed by June 2023. We expect the results to be published by the end of 2023.

**Conclusions:**

This study will be an important step toward evaluating the role of mHealth in improving behaviors related to a healthy diet, supplement use, and promotion of physical activity during pregnancy, as well as in influencing maternal and offspring outcomes. If proven effective, mHealth interventions can be scaled up and included in antenatal care packages at tertiary care hospitals of low- and middle-income countries.

**Trial Registration:**

ClinicalTrials.gov NCT04216446; https://clinicaltrials.gov/ct2/show/NCT04216446

**International Registered Report Identifier (IRRID):**

DERR1-10.2196/31611

## Introduction

### Role of Maternal Diet and Micronutrient Supplement Use

Maternal diet serves as a critical prenatal modifiable factor that influences fetal growth and development. Inadequate consumption of macronutrients (ie, proteins, carbohydrates, and fats) and micronutrients, especially folic acid, iron, calcium, and vitamin D, may influence the programming of the offspring’s organs with health consequences during the life course [1]. Evidence suggests strong associations between maternal undernutrition and fetal growth restriction [2]. Consumption of a Mediterranean-type diet rich in fruits and vegetables produces a remarkable decrease in the risk of preterm birth [3,4], hypertension [5], and gestational diabetes mellitus [6]. Adequate consumption of fish and folic acid has beneficial effects on the prevention of pre-eclampsia and gestational hypertension [7, 8].

Poor nutrition during the sensitive phase of the first trimester of pregnancy not only affects growth in the later trimesters and birth weight [9-11] but could also derange epigenetic programming, resulting in long-lasting health consequences [12]. Subtle variations in nutrition during pregnancy and lifestyle factors may influence the risk of noncommunicable diseases without affecting birth weight [13].

The association of micronutrient deficiencies with unfavorable maternal and fetal outcomes is well established. Maternal anemia accounts for low birth weight (12%), preterm births (19%), and perinatal mortality (18%) [14]. Low serum folate levels and absence of folic acid supplementation are associated with preterm births [15]. Similarly, vitamin D and calcium deficiencies are causally linked to pre-eclampsia, gestational diabetes mellitus, preterm delivery, and low birth weight [16].

### Physical Activity During Pregnancy

In addition to diet and micronutrients, physical activity is also known to influence maternal and fetal outcomes. Regular physical activity is recommended during pregnancy for prevention of gestational diabetes and pre-eclampsia [17,18]. The American College of Obstetricians and Gynecologists (ACOG) recommends at least 150 minutes of moderate-intensity aerobic activity every week, or at least 30 minutes on most days of the week, for pregnant women [17,19]. Aerobic activities involve rhythmic movement of large body muscles, such as those in the legs and arms. Moderate intensity refers to moving enough to raise the heart rate and to sweat while being able to talk normally but not being able to sing [20].

### Maternal Health Status in Pakistan

Women of reproductive age in Pakistan are facing a triple burden of malnutrition. A significant proportion of them are underweight (14.4%), overweight (24%), or obese (13.8%) [21]. In addition, there is a high prevalence of micronutrient deficiency, particularly regarding iron (18.2%), calcium (26.5%), and vitamin D (79.7%) [21]. There is also a substantial burden of high-risk pregnancies, causing such complications as gestational hypertension (6.5%) [22], pre-eclampsia (2.4%) [22], and gestational diabetes mellitus (3.3%-17.2%) [23,24]. Pakistan ranks 4th among the top 10 countries with regard to preterm births (16 per 100 live births) [25] and the prevalence of babies with low birth weight (22%) [26].

Of further concern are the suboptimal nutritional indicators for women living in urban areas, where only 42.2% of them have normal BMI compared to 48.5% in rural areas. A significant proportion of these women suffer from undernutrition (12%), overweight (26.5%), and obesity (17.2%) [21]. Also, vitamin D deficiency is more common in urban (83.6%) than in rural (77.1%) settings [21].

Lately, women in Pakistan, in addition to fulfilling their reproductive responsibilities, have started participating in economic activities to support their careers and families. About 17% of women are employed nationwide, and 21% of women who have ever been married are working in the province of Sindh [26]. When they enter pregnancy as nutritionally compromised, these women are found to further neglect their health due to work and other responsibilities [21]. Further, interventions for improving maternal nutrition in Pakistan have been mainly in the form of supplementation of folic acid, iron, multiple micronutrients, calcium, and iodine, as well as balanced protein-energy supplementation [27].

Given the significant magnitude of maternal undernutrition and adverse perinatal outcomes in Pakistan, there is a need to adopt innovative counseling strategies during the critical antenatal period that would regularly remind women to pay attention to their diet and physical activity needs. This would not only reduce the risk of maternal complications, such as pre-eclampsia, pregnancy-induced hypertension, and gestational diabetes, but would also improve the immediate and long-term health of the newborn.

### mHealth Interventions During Pregnancy

The antenatal period represents a major life event when self-motivation to improve diet and lifestyle is often high. This transition to parenthood provides an incredible opportunity, based on the theory of planned behavior [28], because of the willingness to adapt, keeping in mind the expected benefit of having a healthy baby [29]. Hence, communication strategies using mobile health (mHealth) can serve as an awareness tool for desired adjustment in diet and physical activity through positive reinforcement and by offering practical and evidence-based suggestions.

Smarter Pregnancy is one such mHealth intervention launched among the Dutch population in their local language [30]. It was introduced as an online, device-independent, web-based coaching platform for couples during their periconception and pregnancy periods for dietary improvement, folic acid use, and alcohol and smoking cessation [30]. The program consisted of 6 months of interactive coaching through tailored and personalized short text messages and emails; the program showed high compliance (65%) and usability (55%), as well as significant improvement in diet and lifestyle behaviors [30].

### Emergence of mHealth in Pakistan

Being home to a population of over 220 million, Pakistan is experiencing an enormous increase in the digital landscape that parallels the global increase in internet access (45%) and mobile phone subscriptions (96%) [31]. Nationwide, the proportion of internet users has increased by 17% from 2019, reaching 76.38 million in 2020 [32]. According to the recent Digital Pakistan Policy, the Ministry of National Health Services has received support for the promotion of telemedicine and disease prevention information through information and communication tools [33]. With the potential to reach a great proportion of the population at a low cost [31,34], tailored health promotion messages through new delivery modes, such as the internet and mobile phones, have shown promising effects in improving nutrition, lifestyle, and compliance to medication [34-37].

### mHealth-Related Interventions in Pakistan and the Existing Gap

Recently, a few mHealth initiatives have been introduced, such as the Baby+ app for pregnant women in urban areas [38]; the MotherCare app in Swat District [39]; Marham, a private initiative [40]; and Teeko, an Android-based app for improving childhood immunization in rural Sindh [41]. However, there has been no systematic assessment of any locally developed mHealth apps for pregnant women targeted toward improvement in diet, supplement use, and physical activity.

Using an mHealth platform, we intend to empower pregnant women and their health care providers to identify modifiable dietary and lifestyle inadequacies and to receive personalized coaching to address them.

### Study Objectives

#### Primary Objective

Our primary objective is to assess the efficacy of an mHealth coaching intervention compared to standard face-to-face counseling in improving (1) maternal diet by 30%, (2) supplement use (ie, iron, folic acid, calcium, and vitamin D) by 30%, and (3) physical activity by 20%.

#### Secondary Objectives

Our secondary objectives are to conduct the following:

Investigate the efficacy of the intervention regarding the following:Reducing incidence of gestational diabetes mellitus, gestational hypertension, and pre-eclampsia.Improving mean gestational weight gain and mean weight, length, and gestational age at birth.Improving mean BMI and blood pressure at 1 year of age.Evaluate compliance (ie, completion of the 6-month program) and usability (ie, design and interface, content and coaching, and perception and personal benefit) of the mHealth app among women in the intervention group.

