### Expected Secondary Outcomes

#### Maternal Health

The following four maternal conditions will be identified through the medical records.

Pre-eclampsia will be defined as new onset of hypertension after 20 weeks of gestation along with proteinuria (ie, a spot urine protein to creatinine ratio of ≥30 mg/mmol) and/or evidence of maternal acute kidney injury, liver dysfunction, neurological features, hemolysis or thrombocytopenia, and/or fetal growth restriction [62].

Gestational hypertension will be defined as new onset of hypertension (ie, blood pressure of ≥140 mm Hg systolic or ≥90 mm Hg diastolic at or after 20 weeks’ gestation) [62].

Gestational diabetes will be defined as diagnosis made by a single-step 75-g oral glucose tolerance test conducted between 24 and 28 weeks of gestation or at any other time, with one or more of the following results: (1) fasting plasma glucose of 5.1 to 6.9 mmol/L (92-125 mg/dL), (2) 1-hour post–75-g oral glucose load of ≥10 mmol/L (180 mg/dL), and (3) 2-hour post–75-g oral glucose load of 8.5 to 11.0 mmol/L (153-199 mg/dL) [63].

Due to the expected low incidence of these conditions and given our small sample size, we shall pool these conditions as adverse maternal outcomes.

Gestational weight gain will be determined from weights recorded during the first, second, and third trimesters. Centiles and *z* scores will be assessed using the international gestational weight gain calculator based on the INTERGROWTH-21st (International Fetal and Newborn Growth Consortium for the 21st Century) Project standards for gestational weight gain [64,65].

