### Statistical Analysis

Data will be entered and analyzed using Stata software (version 12; StataCorp LP). Data from the intervention group will be digitalized and uploaded to the app. Categorical variables will be reported as frequencies and percentages. Continuous variables will be reported as means and SDs or medians and IQRs, as appropriate. General characteristics, nutritional change in the form of dietary risk score, supplement use, maternal outcomes, gestational weight gain, birth weight and length, BMI, and blood pressure will be compared using chi-square tests for proportions and *t* tests and Mann-Whitney *U* tests for continuous variables. A mixed-model method will be used to take into account the repeated measurements and correlation while modeling the fraction that scores adequately at each of the follow-up time points. In order to minimize selection bias, we will use multiple imputation models to handle missing data from participants who prematurely leave the study. Possible confounding variables, such as age, BMI, parity, previous history of miscarriage, socioeconomic status, educational status of the women, and occupation, will be assessed and adjusted. Moreover, interactions will be reported if present in the model.

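### The objective of improving mean gestational weight gain has no stated direction or target, so a difference in arm means cannot be labelled benefit or harm

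*Protocol article*

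**What the plan says.** All references are to the protocol article.

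- **Secondary Objectives.** The aim is "Improving mean gestational weight gain and mean weight, length, and gestational age at birth". The next item sets a parallel aim for mean infant BMI at 1 year.
- **Expected Secondary Outcomes, Maternal Health.** "Gestational weight gain will be determined from weights recorded during the first, second, and third trimesters". Then: "Centiles and *z* scores will be assessed using the international gestational weight gain calculator", based on an international standard. No range of adequate gain is given.
- **Statistical Analysis.** Gestational weight gain stands in a pooled list of variables to be compared by chi-square tests for proportions and by t or Mann-Whitney tests for continuous variables. BMI is among the covariates: "Possible confounding variables, such as age, BMI, parity, previous history of miscarriage, socioeconomic status, educational status of the women, and occupation, will be assessed". The analysis is also to adjust for these covariates. The section ends by saying that "interactions will be reported if present in the model".
- **Maternal Health Status in Pakistan.** Background survey figures for urban women are 42.2% with normal BMI, 12% undernourished, 26.5% overweight and 17.2% obese.
- **Enrollment Criteria.** There is no BMI limit.

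**The concern.** To improve a mean, one must know which way is better. The article supplies this for other outcomes. A higher dietary risk score is poorer, the maternal conditions have diagnostic definitions, and infant blood pressure above the 90th centile counts as high risk. Gestational weight gain and infant BMI receive neither a direction nor a threshold.

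In a setting with many women on both sides of normal BMI, no single direction can be taken for granted. Two consequences follow. First, a higher or lower mean in the app arm could be called improvement after the data are seen. Second, if the programme raises gain in some women and lowers it in others, and both changes are desirable, the arm means understate the effect.

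**Working it through.** **The plan's own figures.** No effect size, SD or power is stated for gestational weight gain. The stated 45 and 107 women per group reproduce exactly (20% vs 50% and 36% vs 56%, two-sided 5%, 80% power, continuity-corrected). They concern the primary outcomes and do not bear on this point.

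**Do the planned elements supply a direction?**
- *z scores.* They are signed. A mean z score near zero can come from women close to the standard or from women far above and far below it.
- *Adjustment for BMI.* A BMI main effect improves precision. It still yields one common arm difference and does not separate opposite effects.
- *Interactions.* None is named. The only model the section describes is the mixed model for the fraction scoring adequately at follow-ups, so a BMI-by-arm term for weight gain cannot be assumed.

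**How much could opposite changes offset?**

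Inputs from the article:
- Underweight share *u* = 0.12.
- Overweight or obese share *o* = 0.265 + 0.172 = 0.437.
- 150 women per arm (300 at 1:1).
- 117 per arm after losses (234/2). The losses were uneven, 42 and 24. Assuming 150 per arm at the start, 108 and 126 remain. The equivalent equal size is 2 × 108 × 126 / 234 = 116, so 117 is close enough.

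Assumptions, not in the article:
- The programme shifts each affected woman by *d* SD.
- The SD is 1.
- Women of normal BMI do not shift, except in the last step.
- The trial sample has the survey's BMI mix.

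Formulas:
- Opposite shifts: Δ = (*u* − *o*)*d* = −0.317*d*.
- Same-direction shifts: Δ = (*u* + *o*)*d* = 0.557*d*.
- Ratio of sizes: 0.317 / 0.557 = 0.57, whatever *d* is.
- Power ≈ Φ(|Δ|√(n/2) − 1.96).

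| *d* | Pattern | Size of Δ (SD) | Power, 150 per arm | Power, 117 per arm |
|---|---|---|---|---|
| 0.3 | opposite | 0.095 | 13% | 11% |
| 0.3 | same direction | 0.167 | 30% | 25% |
| 0.5 | opposite | 0.159 | 28% | 23% |
| 0.5 | same direction | 0.279 | 67% | 57% |

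**When would the offset be nearly complete?** With normal-BMI women unchanged, the underweight shift must be 0.437 / 0.12 = 3.6 times the overweight or obese shift. Alternatively, normal-BMI women must also shift up:
- Half of them (0.211): Δ = (0.331 − 0.437)*d*, which is −0.03 for *d* = 0.3 and −0.05 for *d* = 0.5.
- All of them (0.422): Δ = (0.542 − 0.437)*d*, which is +0.03 and +0.05.

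Power with 150 per arm is then about 5% to 7%.

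**The case against.** **The aim can be read neutrally.** The Study Goal asks only whether outcomes differ between groups, and a difference in means answers that. This stands, so it would be wrong to infer that the objective cannot be answered at all. But Secondary Objectives goes further and claims improvement, which a bare difference cannot establish.

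**Opposite effects are not documented.** A reader might infer that the programme's effects must run in opposite directions and cancel. The article does not support this. Its counselling advice is not set by BMI, and no weight-gain target is given. Personalised feedback, and a risk score that penalises both too few portions and too much fat, make opposing effects plausible but no more. One can pick figures that cancel, such as +3 kg and −0.8 kg: 0.12 × 3 − 0.437 × 0.8 = +0.01 kg. Their ratio of 3.75 sits almost on the null ratio of 3.6, and nothing in the article supports either value.

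**BMI category is not adequacy of gain, and the mix is not the trial's.** This also stands. The figures come from a background survey. The trial enrols smartphone owners at a private tertiary hospital and excludes women on dietary control for diabetes or taking certain medications. The article does not report how many women gain too little or too much.

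**Chi-square tests on centile categories would fit the pooled list, and cut-offs or named interactions may sit in an analysis plan that is not shown.** This is fair, and the lack of a band is not in itself the fault. The fault is that the article fixes the mean as the measure and claims improvement in it without saying what improvement is.

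**Conclusion.** The point holds as a defect in how a secondary objective is defined. Whatever its sign, a difference in mean gestational weight gain, raw or as a z score, has no stated reading as benefit or harm. This conclusion needs no assumption about effect sizes, and the planned z scores, BMI adjustment and unnamed interaction do not remove it.

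Loss of sensitivity is a second, conditional consequence. Under equal and opposite shifts at the survey's BMI mix, about 57% of the same-direction difference remains. The power figures also assume *d* and an SD of 1, and serve only as illustration. Near-complete cancellation needs further assumptions, so it should not be presented as expected.

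Infant BMI at 1 year shares the missing direction, though the article does compare it with a sex- and age-adjusted reference. The primary outcomes are unaffected. This is a worthwhile and inexpensive correction.

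**What to change.** 1. Restate the objective as moving gestational weight gain towards the reference standard already named under Maternal Health.
2. Keep the comparison of means. Beside it, prespecify a between-arm comparison of deviation from that standard, using either the mean absolute z score or the proportion within a z-score or centile range. The investigators should choose and record any range before analysis; −1 to +1 would be one example.
3. Show this comparison by enrolment BMI category, with a named BMI-by-arm interaction.
4. State that improvement in infant BMI at 1 year means closeness to the reference named under Infant Health.

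The cost is some rewording and one derived variable per outcome. Maternal z scores are already planned, and BMI is already an adjustment variable. A proportion within a range loses some precision through dichotomising, which the mean absolute z score avoids. The interaction will be imprecise at this sample size and is best reported as an estimate with its interval.

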## Methods

### Target Population

Our target population is pregnant women in their first trimester from the urban area of Karachi, Pakistan.

### Study Goal

Our study goal is to assess the role of the mHealth program in improving the behaviors of pregnant women related to diet, supplement use, and physical activity. In addition, we are interested in assessing whether the maternal, newborn, and infant outcomes differ between those who use the program compared to those who do not.

### Study Hypothesis

We hypothesize that the mHealth coaching program will be effective in improving diet and supplement use among pregnant women by 30% and physical activity by 20% during the study period.

